**Methods:**

The protocol is designed as a triple-blind randomized, controlled, parallel-group clinical trial in children aged 5–14 years. The study should have been carried out from August 2021 to August 2024 in Zanskar Valley (Ladakh), but the COVID-19 pandemic does not allow today to make predictions on the exact start. Participants will be randomly allocated into two groups: subjects who will receive a chewing gum with Xylitol (70% w/v) as only sweetener, and those who will receive a sugared chewing gum containing Maltitol (23% w/v). The subjects will be instructed to chew a total of 6 pellets for 5 min divided into 3 intakes a day (2 in the morning, 2 after the midday meal and 2 in the afternoon) for one school year. Clinical examination will comprise an oral examination in which caries index (ICDAS scores), bleeding on probing and plaque pH evaluation after sucrose challenge will be recorded at baseline (*t*_0_); the clinical examination will be repeated after 12 months since the beginning of the chewing gum administration period (*t*_1_), after another 12-month period (*t*_2_) and finally after further 12 months (*t*_3_) (24 months from the end of the chewing gum use). The primary outcome will be the caries increment measured both at enamel and dentinal levels on primary and permanent molars. Data analysis will be conducted through Kaplan-Meyer graphs to evaluate caries increment. A comparison of the methods will be carried out with Cox regression with shared frailty. The net caries increment for initial, moderate and severe caries levels, using ICDAS (Δ-initial, Δ-moderate and Δ-severe), will be calculated.

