### Outcomes

The primary outcome will be the caries increment measured both at enamel and dentinal levels. The secondary outcomes will be the differences obtained comparing caries increment and the variation of plaque pH in relation to the treatment used. Furthermore, a cost-effectiveness analysis will be performed using as outcome the measurement of quality-adjusted life years (QALY) [21].

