### Data collection, management, and analysis

The follow-up assessments will be performed by calibrated blinded dentists. The clinical data will be recorded on electronic sheets organized on PageMaker and then transferred into Microsoft Excel Software. The data management team is formed by two authors ([name], [name]). Data will be cleaned, deleting those revealing the participants’ identities, and they will be shared in a public repository at the moment of the submission of the manuscripts.

Data on caries will be recorded considering the tooth as the unit of analysis. The progression or change of status can be described with three modalities: 1—as the change from no caries stage to initial stage or to moderate stage or extensive; 2—as the change from initial stage to moderate or extensive stage; and 3—as the change from moderate stage to extensive stage. The net caries increment for initial, moderate and extensive caries levels, using ICDAS (Δ-initial, Δ-moderate and Δ-extensive), will be calculated in primary and permanent molars. Differences between groups in terms of caries increment will be evaluated using the nonparametric Mann–Whitney *U* test. Data analysis will be conducted through Kaplan–Meyer graphs to evaluate caries increment. A comparison of the methods will be carried out with Cox regression with shared frailty. The calculation of sensitivity, specificity and accuracy will consider the results obtained with the indices and the classification of caries lesion presence by the proposed reference standard. The cost-effectiveness ratio will also be verified, considering as effectiveness the prevention of the primary outcome. For all tests, two-tailed analyses will be used, considering a level of significance of 5%. The quality-adjusted life-year index (QALY) will be calculated to assess the value of the preventive intervention [22]. To determine QALYs, the utility value associated with a given state of health by the years lived in that state will be calculated. A year of life lived with no caries increment will be worth 1 QALY (1 year of life × 1 utility value) [22, 23]. Plans to promote participant retention and completion of follow-ups will be performed; a list of any outcome in participants who discontinue the treatment will be compiled and the data will be analysed, taking into account that living conditions in Ladakh do not allow for high mobility of the population. This will make participant retention a minor problem.

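### The primary outcome is not one quantity: caries increment spreads over three to six level-specific measures and two methods, each test at 5%, and the same comparison recurs as a secondary outcome

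*Protocol article*

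**What the plan says.** All references are to the protocol article.

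- **Primary outcome.** The Outcomes section states: "The primary outcome will be the caries increment measured both at enamel and dentinal levels". The abstract's Methods paragraph adds the dentitions: "The primary outcome will be the caries increment measured both at enamel and dentinal levels on primary and permanent molars".
- **Derived measures.** The section on data collection, management and analysis introduces "The net caries increment for initial, moderate and extensive caries levels, using ICDAS", three deltas that "will be calculated in primary and permanent molars". It does not say whether the two dentitions are pooled or kept apart, and it does not define net.
- **Methods.** "Differences between groups in terms of caries increment will be evaluated using the nonparametric" Mann–Whitney test, with no level, dentition or visit named. Then: "A comparison of the methods will be carried out with Cox regression with shared frailty". Neither method is ranked above the other.
- **Error rule.** "For all tests, two-tailed analyses will be used, considering a level of significance of 5" per cent.
- **Secondary outcome.** "The secondary outcomes will be the differences obtained comparing caries increment and the variation of plaque pH", by treatment.
- **Time.** Implementation sets follow-up examinations at 12, 24 and 36 months and calls none of them primary. Sample size refers to results over three years. The event definition at the end of the analysis section refers to a follow-up of two years.
- **Event definition.** For the event rate and number needed to treat, an event is a new lesion, a progressed lesion, or an affected tooth that becomes filled or missing.

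**The concern.** A superiority trial needs one comparison on which its claim stands or falls. Here the named outcome becomes several measures, two methods and three possible time points, each test may use the full 5%, and no order is given. If one increment is significant and another is not, the plan does not say which result counts. The secondary list does not separate the roles either, because it contains the same between-treatment comparison of caries increment.

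The second worry is direction. Each tooth is recorded at one severity level. If a level's net increment is simply the change in the number of teeth at that level, a tooth that worsens from initial to moderate leaves the initial count. A lower initial increment would then not necessarily mean less disease.

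**Working it through.** **1. The plan's own figure.** The Sample size section gives 409 subjects for about 90% prevalence, a 10-point difference, two-sided 0.05 and 80% power (Kelsey). With 90% v 80%, the mean proportion is 0.85, and

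n per arm = (1.960 + 0.842)² × 0.85 × 0.15 × 2 / 0.10² = 200.1,

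so 402 in total. That is close to 409. Adding the stated increase of about 10% gives 402 × 1.1 = 442.2, or 443, so 409 is not reproduced with the increase. That gap does not bear on this point. What matters here is that the calculation covers **one** binary contrast, which is none of the level-specific increments.

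**2. How many tests.** Three levels × one pooled dentition = 3. Three levels × two dentitions = 6. Both counts are for one visit and one method.

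**3. Chance of at least one p<0.05 with no effect.** For independent tests this is 1 − 0.95^m. For correlated tests it was simulated with equally correlated normal test statistics (200,000 draws). The correlations are assumptions; the article gives none.

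| Correlation | 3 tests | 6 tests |
|---|---|---|
| 0 | 14.3% | 26.5% |
| 0.3 | 13.6% | 24.2% |
| 0.5 | 12.6% | 20.9% |
| 0.7 | 11.0% | 16.2% |
| 0.9 | 8.4% | 10.7% |

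Simulated Mann–Whitney tests on level-specific increments (204 children per arm, no clustering, two independently simulated dentitions) gave 12% for three tests and 23% for six, inside these ranges. The errors are two-sided. The chance of at least one false result favouring Xylitol, for independent tests, is 1 − 0.975³ = 7.3% or 1 − 0.975⁶ = 14.1%, about half of the figures above. One two-sided test would give 2.5%.

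**4. Direction of the initial increment, if net means change at exactly that level.** Suppose 20 new initial lesions arise in each arm, with 10 progressing from initial to moderate in one arm and 30 in the other.

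- Initial increment: 20 − 10 = +10 v 20 − 30 = −10. The arm with more progression looks better.
- Moderate increment (no exits from moderate): +10 v +30. That arm looks worse.
- Initial or worse, counted cumulatively: +20 v +20. The reversal is gone.

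A simulation used assumed rates: 8 molars per child; baseline 40/30/15/15% sound, initial, moderate, extensive; 20% sound-to-initial and moderate-to-extensive in both arms; initial-to-moderate 20% v 35%. The expected values per child are:

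- teeth progressed: 8 × (0.08 + 0.06 + 0.03) = 1.36 v 8 × (0.08 + 0.105 + 0.03) = 1.72;
- initial increment: 8 × (0.08 − 0.06) = +0.16 v 8 × (0.08 − 0.105) = −0.20.

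The worse arm was significantly lower on the initial increment in 87% of 1,000 runs. With the cumulative count, a significant difference appeared in 4% of runs, about the nominal level.

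**5. Cost of splitting alpha instead.** On the plan's 90% v 80% contrast with 409 subjects and no clustering, power is 81% for one test at 5%. It is 67% with Bonferroni over three and 58% over six. Restoring 80% would take about 532–534 or 616–618 subjects, before any increase or allowance for clustering.

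**The case against.** A condensed article commonly leaves test order and the exact derivation of endpoints to an analysis plan, and a general 5% statement does not forbid a later hierarchy. That is fair as far as it goes. But the article does not merely stay silent: it assigns 5% to every test, and its Outcomes section places one comparison under both primary and secondary.

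Three stronger readings are tempting, and the text does not support them.

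- **At least six separate primary tests.** The deltas are calculated in both dentitions, but nothing says they are tested separately by dentition. Pooling gives three, so six is not a lower bound. Nor does any sentence say that one significant increment is enough for success.
- **A 60% error rate.** Six increments at three visits would give 1 − 0.95^18 = 60%. The article lists examination dates, not a test at each visit, and a survival analysis can use all visits at once. Independence is also implausible for repeated findings on the same teeth.
- **The worse arm would win.** The reversal needs one particular meaning of net. The same section first describes change as upward transitions, and its event definition counts progression as an event. Increments built on those have no reversal. Even on the unfavourable meaning, the moderate increment would move the other way and expose the conflict. What stands is that net is undefined and no rule resolves such a conflict.

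The Cox sentence speaks of comparing methods; it is read here as comparing the arms. If it means something else, the counts of three and six are unaffected, since they use one method only.

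**Conclusion.** The point holds in this form: the article does not fix a single deciding increment, visit or method, it gives every test two-sided 5%, and it repeats the comparison of caries increment as a secondary outcome. Under no effect, the chance of at least one p<0.05 is about 8–14% for three tests and 11–26% for six, with about half favouring Xylitol. These ranges assume equal correlations between 0.9 and 0, one visit and one method. They ignore clustering by class and child. The direction problem is conditional: it arises only if net means change in the number of teeth at exactly one level, and on that meaning it conflicts with the article's own event definition. The simulated 87% illustrates that reading under assumed rates and is not a forecast. This should be corrected before recruitment; it does not show that the trial would reach a wrong conclusion.

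**What to change.** - **Name one primary comparison at two-sided 5%.** The article's own event is a ready candidate, taken across both dentitions: a new or progressed lesion, or an affected tooth becoming filled or missing.
- **Name one method.** The planned Cox model with a shared frailty would serve, provided the frailty or the variance accounts for the randomised class. Choosing between a count and a hazard must not be left open, since that would again leave two tests.
- **Name one horizon.** First reconcile the three-year period in the Sample size section with the two-year period in the event definition.
- **Define net.** Make the level-specific increments cumulative (initial or worse, moderate or worse, extensive) so that progression cannot reduce them.
- **Rank the rest.** Make the level- and dentition-specific results secondary, reported with confidence intervals or tested in a fixed order, and delete caries increment from the secondary list.

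This changes wording only, and the Trial status section says recruitment has not begun. The cost is that fewer results can be called confirmatory. A single primary test avoids the loss of power that splitting alpha would bring, although the 81% shown above belongs to the plan's binary contrast without clustering and not to the Cox event.

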#### Preliminary epidemiological survey

A team of four dentists received training to diagnose caries lesions using the WHO-DMFT index for permanent teeth and the dmft for primary teeth. The team received training, and inter-examiner reliability was assessed before the start of the study; sensitivity, specificity, percentage agreement and kappa statistics were recorded. Inter-examiner reliability ranged from 0.75 to 0.84 (K-Cohen) for sound teeth and from 0.82 to 0.88 for caries lesions. Intra-examiner reliability ranged from 0.82 to 0.90 for sound teeth and from 0.84 to 0.91 for caries lesions. Dental caries prevalence (dt/DT) and severity (number of lesions) were recorded for caries at the dentinal lesion level [12]. Every subject was examined using a plain mirror (Hahnenkratt, Königsbach, Germany) and the WHO CPI ballpoint probe (Asa-Dental, Milan, Italy), under standard light. No bitewing radiographs or fibre-optic trans-illumination were used.

An ad hoc prepared questionnaire assessed general health, eating habits, oral hygiene and the self-perception of oral conditions, based on previous surveys [12, 13]. The height (cm) and the weight (kg) were measured and the body mass index (BMI) was calculated. The waist circumference was also measured.

Caries was almost ubiquitarian with only 10.04% of caries-free children (dt/DT = 0). Caries severity, in both primary and permanent dentitions, was statistically significantly related to gender and waist circumference (*p* < 0.01). This preliminary epidemiological survey will allow to design the intervention trial.

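### The QALY rule ties full health to the absence of change, so in a population with about 90% existing caries it counts increment-free years, not QALYs

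*Protocol article*

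**What the plan says.** In the Protocol article, section Data collection, management, and analysis, the general rule multiplies a utility by time: "the utility value associated with a given state of health by the years lived in that state will be calculated". The next sentence fixes one utility: "A year of life lived with no caries increment will be worth 1 QALY". A bracket after it explains this as one year times a utility of 1.

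The Outcomes section makes this quantity the result of the economic analysis: "a cost-effectiveness analysis will be performed using as outcome the measurement of quality-adjusted life years (QALY"). The data section also plans a second economic measure in natural units: "The cost-effectiveness ratio will also be verified, considering as effectiveness the prevention of the primary outcome".

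On existing disease, the Preliminary epidemiological survey section reports: "Caries was almost ubiquitarian with only 10.04% of caries-free children". That figure refers to lesions at the dentinal level.

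**The concern.** The two consecutive sentences on QALYs do not fit together. The first attaches utility to a state of health. The second attaches the top of the utility scale to an event not happening. A child with several extensive lesions that stay as they are for a year scores the same as a child with sound teeth.

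In a population with little disease this would be a minor approximation. Here nearly all children are expected to start with caries, so the approximation applies to almost every child-year. The result would carry the name of a QALY and invite comparison with QALYs from other programmes, although it measures something else. Depending on how the remaining utilities are set, the QALY gain from preventing an increment could also be too large, and the cost per QALY too low.

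**Working it through.** **Inputs**
- Utility of a year without an increment: 1 (Data collection, management, and analysis).
- Children free of dentinal caries: 10.04%, so 100 − 10.04 = 89.96% have it, rounded to 90% (Preliminary epidemiological survey). I assume that this share carries over to the trial's child-years.
- s, the utility of a stable year for a child with existing caries: not in the article; assumed.
- u, the utility of a year with an increment: not in the article; assumed.

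**Step 1. The stated figure.** 1 year × utility 1 = 1 QALY. This reproduces.

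**Step 2. Level.** If utility follows the child's state, the mean utility of an increment-free year is 0.10 × 1 + 0.90 × s.
- s = 0.95: 0.10 + 0.855 = 0.955
- s = 0.90: 0.10 + 0.81 = 0.91

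The stated rule gives 1 in both cases.

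**Step 3. Contrast, with u set as an ordinary state utility.** For a child with existing caries, an increment costs s − u when utility follows state, and 1 − u under the stated rule. With u = 0.90:

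| s (assumed) | State-based loss, s − u | Stated rule, 1 − u | Ratio |
|---|---|---|---|
| 1.00 | 0.10 | 0.10 | 1 |
| 0.95 | 0.05 | 0.10 | 2 |
| 0.91 | 0.01 | 0.10 | 10 |

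The number of increment years prevented multiplies both columns equally, so the ratio does not depend on the treatment effect. The table is for a carious child. For a caries-free child the loss is 0.10 either way. If prevented increments fell on the two kinds of child in the survey proportions, with the same u, the average state-based loss in the last row would be 0.10 × 0.10 + 0.90 × 0.01 = 0.019, and the ratio 0.10 / 0.019 = 5.3.

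**Step 4. Contrast, with the increment set as a decrement D.** The state-based loss is s − (s − D) = D. The stated rule gives 1 − (1 − D) = D. The two agree whatever s is.

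So the level is wrong in either case. The difference between arms is wrong only if increment years are valued as in Step 3, which is what the article's own general rule describes.

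**The case against.** The best defence is Step 4. With randomised arms and a common decrement for an increment, the value given to a stable year drops out of the comparison. That is correct, but it needs a convention that the article does not state. Its general rule values states, not decrements.

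A second defence is that a journal article need not print every utility. This also stands. A reader might infer that the cost per QALY is arbitrary because no utility is given for a year with an increment, and might support this with the gain formula 0.10 × (1 − u), which runs from 0.10 at u = 0 to 0.001 at u = 0.99, a 100-fold range. The documents do not support that reading. Utilities for health states are foreseen in general terms and may be set in a fuller plan. Nothing assigns 0 to a year with an increment. The 10% absolute difference in the Sample size section is set against a prevalence of about 90% and 3-year results, so it is not a yearly rate.

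Neither defence repairs the sentence that equates no increment with a utility of 1. Extra detail elsewhere cannot correct a value that is already fixed.

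It is also fair to say that the article keeps a cost-effectiveness ratio in natural units, "considering as effectiveness the prevention of the primary outcome", so a usable economic result survives.

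**Conclusion.** The point holds in a limited form. The article contradicts its own definition of utility by giving full health to every year without an increment, in a population where about 90% of surveyed children had dentinal caries. The quantity is increment-free years and should not be called a QALY.

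The size of any overstatement cannot be fixed from the article. It is nil if increments are valued as decrements from the stable state. It is 10-fold for a carious child under the assumed utilities of 0.91 and 0.90, and 2-fold if the stable year is worth 0.95 instead of 0.91. These are illustrations, not estimates.

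The conclusion does not rest on the absence of a utility for increment years. It concerns the economic analysis only and does not touch the primary caries comparison. Because cost-effectiveness is a stated outcome, the wording should be corrected.

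**What to change.** - In Outcomes and in Data collection, management, and analysis, make the cost-effectiveness ratio based on prevention of the primary outcome the main economic measure. The article already plans it.
- State the unit of that ratio. The article takes the tooth as the unit of analysis and defines events at tooth level, so a ratio per child would be a new specification and must be written as one.
- Relabel the present QALY as increment-free years.
- Keep a QALY only as a sensitivity analysis, with utilities set in advance for each caries state, including existing disease, and with a stated range.

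This changes wording only and needs no new data. According to the Trial status section recruitment has not begun, so it can be done before any outcome is seen. The price is that the main economic result can no longer be set against a QALY threshold, a comparison that the current rule does not support.

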## Methods

### Trial design

This is the third and final version of the protocol (edited on the 15th of May 2021). A superiority trial is designed to detect a difference between treatments as a triple-blind randomized, controlled, parallel-group clinical trial. Two groups will be compared: subjects who will receive a Xylitol chewing gum with the polyol as the only sweetener (70% w/v), and those who will receive sugared gum containing a 23% (w/v) Maltitol. The flowchart of the study design is displayed in Fig. 1.

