### Interventions

After obtaining actual caries data, schools with similar numbers of schoolchildren (at least 300 subjects per school) will be selected for the preventive project. The participants will be randomized, taking as cluster the school class, allocating each class into one of the two groups of the study (Fig. 1):

(1) The first group (Xyl) will receive sugar-free gums containing 70% (w/v) Xylitol as the only sweetener

(2) The second group (Pol) will receive reduced sugared gums containing 23% (w/v) Maltitol

Both groups of children will receive a total of 6 pellets of chewing gum a day during a period of one school year (about 9 months). All chewing gums will be produced and supplied by Perfetti Van Melle SpA (Lainate, Italy). All types of chewing gums will weigh 1.4 g each and will be identical in colour, shape and taste.

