#### Treatment

[name] will coordinate the treatment phase of the chewing gums. The subjects of both arms will be instructed to chew a total of 6 pellets for 5 min divided into 3 intakes a day (2 in the morning, 2 after the midday meal and 2 in the afternoon) [7, 8]. Thus, the total daily intake of Xylitol in the Xyl group will be 5.8 g, whilst, in the Pol group, the amount of administered Maltitol will be 1.9 g. Subjects will be instructed to use the chewing gum immediately after the main meals and snacks. Parents/guardians will not be requested to make changes in the dietary and oral hygiene habits of their children. Tooth brushing will not be allowed for at least 1 h after the chewing gum use. All subjects will receive a fluoridated toothpaste containing 1450 μg/g NaF and a manual toothbrush, which will be substituted every 3 months throughout the entire experimental period (3 years). All children will be instructed to brush their teeth twice a day (after breakfast and dinner) for 2 min using vertical movements [20].

In order to evaluate the success of the administration of chewing gum at school, teachers will receive 1 month at a time the chewing gums necessary for that period of time and will distribute the blister packs to their school class. Children will have to return their empty blister pack when receiving that for the following month. This procedure will be repeated for all experimental (chewing) period (1-year school calendar/9 months).

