The effectiveness of the treatment will be assessed for those who fully followed the protocol (per-protocol subjects). The efficacy and consequences of treatment will be also considered, calculating the event rate (ER) for each group and the number needed to treat (NNT) [24]. An event will be defined as the change of status at tooth level, i.e. the development of a new lesion or the progression of an existing lesion to a more severe level or the change of a tooth previously affected in a filled or a missing tooth during the 2-year follow-up period.

Analyses will be performed using the statistical package Stata 16.0 (Stata Corp, College Station, USA).

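### Effectiveness in a class-randomised superiority trial is assigned to children who fully followed the protocol, and no all-randomised comparison is named

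*Protocol article*

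**What the plan says.** The Trial design section sets the objective: "A superiority trial is designed to detect a difference between treatments as a triple-blind randomized, controlled, parallel-group clinical trial". The Interventions section makes the school class the unit of randomisation. The Data collection, management, and analysis section then contains three statements on who is analysed:

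- On effectiveness: "The effectiveness of the treatment will be assessed for those who fully followed the protocol (per-protocol subjects", closing the parenthesis there. No definition or threshold for full adherence follows.
- On event rate and number needed to treat: "The efficacy and consequences of treatment will be also considered, calculating the event rate (ER) for each group and the number needed to treat (NNT"). No population is attached.
- On children who stop treatment: "a list of any outcome in participants who discontinue the treatment will be compiled and the data will be analysed". It is not said that they stay in the randomised comparison.

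The same section lists a Mann–Whitney test, Kaplan–Meier curves and a shared-frailty Cox regression for caries increment, again with no population. The terms intention-to-treat, all-randomised and full analysis set appear nowhere in the article.

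**The concern.** In a superiority trial the main comparison normally rests on the groups that randomisation formed. Full adherence is a behaviour observed afterwards, and here it is demanding: six pellets a day in three intakes for about nine months.

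The article itself gives reasons to think that adherence and caries risk could be linked. The Introduction reports that caries severity in this population was related to oral hygiene frequency and to self-reported chewing problems. A child with trouble chewing may well find a gum regimen harder to keep up. The Treatment section also contains brushing instructions, so following the whole protocol, read literally, could select on oral hygiene. These links are inferences, not findings of the article.

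Two things are at stake. One is validity: if different kinds of children adhere in the two arms, the per-protocol contrast mixes the gum effect with a difference in baseline risk. The other is relevance: the stated aim is a school-based programme to reduce caries incidence, and a result among full adherers does not show what such a programme achieves across the children who are offered it.

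**Working it through.** **1. The plan's own figure.** Inputs from Sample size: two-sided 5%, 80% power, prevalence about 90%, absolute difference 10%, Kelsey method, 409 children. Assumed: 90% vs 80% and equal allocation.

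n per arm = (z₀.₉₇₅ + z₀.₈₀)² × p̄(1−p̄) × 2 / d² = (1.960 + 0.842)² × 0.85 × 0.15 × 2 / 0.10² = 200.1, so 201 per arm and 402 in total.

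The stated 409 is within 2% of this (409/402 = 1.017). Adding 10% would give 442, so 409 matches the base calculation. The article attributes its 10% increment to changes in prevalence, not to non-adherence.

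**2. Possible bias, illustration A.** The article gives no adherence figures, so every input here is assumed. There is no true gum effect. Half the children are low-risk (70% event) and half high-risk (95%). Adherence is 80% in both risk groups on the control gum; on xylitol it is 80% in low-risk and 50% in high-risk children.

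- All randomised, either arm: (0.70 + 0.95)/2 = 82.5%; difference 0.
- Per-protocol, control: (0.5×0.8×0.70 + 0.5×0.8×0.95)/0.80 = 0.66/0.80 = 82.5%.
- Per-protocol, xylitol: (0.5×0.8×0.70 + 0.5×0.5×0.95)/0.65 = 0.5175/0.65 = 79.6%.
- Spurious difference: 2.9 points.

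**3. Possible bias, illustration B.** Again assumed, no true effect, with an overall rate near the 90% in Sample size. Children who adhere easily have risk 0.86 and the rest 1.00. In one arm only the easy adherers, 70% of children, adhere; in the other, 85% or 90% do.

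- All randomised, either arm: 0.70×0.86 + 0.30×1.00 = 0.902; difference 0.
- Per-protocol, 70% arm: 0.860.
- Per-protocol, 85% arm: (0.70×0.86 + 0.15×1.00)/0.85 = 0.885; difference 2.5 points.
- Per-protocol, 90% arm: (0.70×0.86 + 0.20×1.00)/0.90 = 0.891; difference 3.1 points.

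Swapping the arms reverses the sign.

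**4. When the bias vanishes.** If xylitol adherence in illustration A were 80% and 50% in both arms, each per-protocol rate would be 79.6% and the difference 0. What matters is whether the same type of child adheres in each arm.

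**5. Power under each population.** Power = Φ{[d√n − 1.96√(2p̄(1−p̄))] / √(p₁(1−p₁) + p₂(1−p₂))}, with n per arm and clustering ignored. The per-protocol column keeps the 10-point effect in fewer children. The all-randomised column keeps 204.5 per arm and shrinks the effect in proportion to adherence (assumed).

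| Full adherence (assumed) | Per-protocol children | Per-protocol power | All-randomised power | Total for 80% power, all randomised |
|---|---|---|---|---|
| 100% | 409 | 0.811 | 0.811 | 398 |
| 90% | 368 | 0.768 | 0.736 | 480 |
| 80% | 327 | 0.719 | 0.646 | 590 |
| 70% | 286 | 0.660 | 0.545 | 746 |

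Per-protocol power falls with adherence, but all-randomised power falls further under this dilution model.

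**The case against.** The strongest reply is that the article does not say every analysis is per-protocol. The Mann–Whitney, Kaplan–Meier, Cox and event-rate analyses carry no restriction, and data on children who discontinue are to be analysed. A reader might infer that effectiveness is assessed only in adherers; the text does not say so, and the sets for the unlabelled analyses may be defined in a document not shown. This stands as a limit on the wording. It does not remove the point, because the one population stated is per-protocol and it is tied to effectiveness.

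A reader might also infer that returned blister packs define full adherence. The Treatment section does say "Children will have to return their empty blister pack when receiving that for the following month", but as a check on how the gum is administered at school. Nothing links it to the per-protocol set, which could be strict or lenient.

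Third, differential adherence may be small. The gums are to be identical in colour, shape and taste, teachers hand them out by class, and children, parents and teachers are blinded. These features lessen the risk but cannot exclude it: the gums differ in composition, and the Harms section plans to ask about side effects of both.

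Finally, a reader might count the loss of power in a per-protocol set as a reason to change. The table in the working shows that it is not one.

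**Conclusion.** The point holds in this form: a stated rule assigns the effectiveness assessment of a randomised superiority trial to children selected by behaviour after randomisation, and no all-randomised comparison is named. That comparison can be biased, and it does not answer the programme question.

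The documents do not support saying that the result will be biased or that it will favour xylitol. The 2.5 to 3.1 points, about a quarter to a third of the 10-point design difference, rest wholly on assumed adherence patterns and child-level event rates. Under other patterns the bias is zero or reversed. The case rests on validity and on the question asked, not on power. The matter should be settled before data are seen; according to Trial status, recruitment has not begun.

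**What to change.** State in Data collection, management, and analysis that the primary comparison of caries increment includes every enrolled child in the arm to which the class was randomised, regardless of gum use, using all available examinations. Keep the per-protocol analysis as a labelled sensitivity analysis, with an adherence definition fixed in advance. State which population the Mann–Whitney, Cox and event-rate analyses use.

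The text change is a few sentences. Little extra data collection should be needed, since outcomes of children who discontinue are already to be compiled and the article says of its setting: "This will make participant retention a minor problem". The real cost is dilution: the estimated effect may be smaller, and if full adherence were as low as 70 to 80%, 409 children would give all-randomised power of about 0.55 to 0.65 under proportional dilution, before clustering. The sponsor should state an expected adherence and check the sample size against it.
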